## Abstract

Playing sports remains one of the most common avenues for youth engagement in physical activity. Yet mental health challenges, such as performance anxiety, depressive symptoms, reduced motivation, and burnout, place many young athletes at risk. As key mediators of sport participation, coaches’ roles are often underscored in recognizing shifts in athlete motivation, behavior, or well-being. Gaining better insight into athlete mental health status may enable coaches to provide timely support and strengthen athlete and team well-being. In this study protocol, we employ a mixed-methods design, evaluating the effectiveness of an AI-augmented mobile application (i.e., ThriveNudge) in promoting the mental health of youth athletes. ThriveNudge helps coaches monitor athlete mental health, flag mood disruptions, and practice supportive communication via simulated chats. A target sample of four interscholastic teams (with athletes aged 14–18 years) and their head coaches will be recruited. Teams will be cluster-randomized to either the intervention condition (*n* = 2), receiving pre-season training to implement ThriveNudge, or to a waitlist control condition (*n* = 2). Primary outcomes, including athlete burnout, motivation, coach–athlete relationships, and sport enjoyment, will be measured using psychometric scales administered online. Semi-structured interviews will be conducted with coaches and athletes in the experimental group to collect qualitative data on user interface and user experience. We hypothesize that teams using ThriveNudge will report lower athlete anxiety and burnout, higher intrinsic motivation and enjoyment, and stronger coach–athlete relationships than athletes in control teams. We aim to provide a scalable and accessible digital platform that safeguards youth mental health.

## 1. Introduction

A growing body of research has established the youth mental health crisis as a pressing public health concern ([Bibr B36-behavsci-16-00268]). Between the ages of 10 and 25, young people undergo rapid biological, social, and emotional changes ([Bibr B22-behavsci-16-00268]). During this developmental period, the onset of common mental health disorders, including anxiety and depression, represents a major contributor to the global burden of disease in youth ([Bibr B37-behavsci-16-00268]). In the United States, the prevalence of identified mental health conditions has increased, with 40% of children meeting criteria by age 18 ([Bibr B36-behavsci-16-00268]). Rising mental ill-being has also been linked to premature mortality, including suicide and physical illness, among young people ([Bibr B22-behavsci-16-00268]). Youth sport participation, meanwhile, has been associated with formative experiences during this transformative period of development ([Bibr B10-behavsci-16-00268]). Yet the current sport landscape has not fully leveraged technological advances, such as artificial intelligence (AI), to support sport as a scalable mechanism for reducing youth mental health burden. In the current study, we propose a protocol to test the efficacy of ThriveNudge (hereafter TN), an AI-augmented digital platform designed to safeguard youth athlete mental health. TN is a non-commercial, research-developed mobile app prototype that facilitates coach–athlete communication and helps coaches foster autonomy-supportive interactions.

Sport-based approaches such as TN build on the idea that well-being can be supported through resources embedded in youths’ everyday settings. Youth sport programs can foster psychosocial skill development ([Bibr B8-behavsci-16-00268]), and the social climate of these settings can shape young people’s satisfaction of basic psychological needs ([Bibr B40-behavsci-16-00268]). When appropriately designed, sport environments can support youth social and emotional well-being by strengthening positive relationships and self-esteem ([Bibr B37-behavsci-16-00268]). Accordingly, research has consistently linked adolescent sport participation with higher levels of life satisfaction ([Bibr B13-behavsci-16-00268]). Among high school students, physical activity has been associated with better mental health and lower psychological distress ([Bibr B15-behavsci-16-00268]). Further, research shows that youth who build skills to sustain self-esteem and cultivate positive relationships are better positioned to carry positive outcomes of sport participation from childhood into young adulthood ([Bibr B38-behavsci-16-00268]).

The extent to which sport supports youth well-being often depends on the environment, particularly the relational context created by coaches. In youth sport, the quality of the coach–athlete relationship is positively associated with athletes’ need satisfaction and well-being ([Bibr B7-behavsci-16-00268]; [Bibr B20-behavsci-16-00268]). Research indicates the importance of a team environment characterized by trust, support, and autonomy in meeting athletes’ developmental needs ([Bibr B4-behavsci-16-00268]). When young athletes perceive low levels of care and support, they may be more likely to report stress, burnout, reduced motivation, and negative peer interactions ([Bibr B10-behavsci-16-00268]). In contrast, coaches can help cultivate caring, autonomy-supportive climates through regular check-ins that support athletes’ basic psychological needs ([Bibr B18-behavsci-16-00268]).

Recent technological advances also present an underutilized opportunity to strengthen coach–athlete relationships and support athlete well-being. Many existing tools primarily facilitate logistics, such as schedule alerts and administrative updates. Other platforms, including AthleteTalk ([Bibr B1-behavsci-16-00268]) and Dailyhuman ([Bibr B5-behavsci-16-00268]), enable athletes to track performance, access strategies for physical or emotional resilience, and monitor aspects of mental health. Yet comparatively few solutions are designed to support coaches directly by building their communication skills, strengthening relationships, and embedding athlete well-being into everyday interactions within sport settings.

TN is an app designed to strengthen coach–athlete relationships by supporting a sport climate that meets youth athletes’ basic psychological needs. Development was informed by Self-Determination Theory (SDT), with features that support intrinsic motivation ([Bibr B33-behavsci-16-00268], [Bibr B34-behavsci-16-00268]). The design premise is that need-supportive communication in sport is central to young athletes’ growth, development, and well-being ([Bibr B7-behavsci-16-00268]). In TN, athletes complete brief daily well-being reflections that are summarized for coaches as scaled check-in indicators and can be viewed across coach-selected time windows. Coaches also interact with integrated large language models (LLMs) that simulate conversations with athletes experiencing varying levels of anxiety and motivation, allowing coaches to rehearse responses and receive prompts aligned with autonomy-supportive communication. These components are intended to strengthen coaches’ need-supportive behaviors and improve athletes’ perceptions of relationship quality and support, which have been associated with greater satisfaction of competence and relatedness needs ([Bibr B7-behavsci-16-00268]). Perceived support has also been linked to positive health outcomes, including stronger coping in stressful situations and lower depressive symptoms ([Bibr B8-behavsci-16-00268]).

Meanwhile, emerging evidence suggests that AI-enabled simulations can support skill development and training outcomes across applied settings. For example, one study used AI-generated simulated patients to train students in clinical interviewing, highlighting the advantages of scalable delivery and opportunities for repeated practice in training contexts ([Bibr B9-behavsci-16-00268]).

The purpose of the present study protocol is to preliminarily evaluate the effectiveness of TN as an AI-augmented tool intended to support youth athletes’ well-being. The protocol also examines implementation in an interscholastic setting, with attention to need-supportive communication, coach–athlete relationship quality, and student-athletes’ well-being and sport experiences over the course of a season. Given the pilot nature of the study and the limited number of clusters, analyses will emphasize descriptive and estimation-focused approaches rather than confirmatory hypothesis testing. Exploratory research questions (RQ_1–4_) are listed below:

RQ_1_: What patterns of change across the season are observed in student-athletes’ sport satisfaction, intrinsic motivation, mental well-being, and burnout among TN teams compared with waitlist control teams?

RQ_2_: How do student-athletes’ perceptions of autonomy-supportive coaching behaviors vary over time between TN teams and waitlist control teams?

RQ_3_: What patterns of change in coach–athlete relationship quality are observed across the season between TN teams and waitlist control teams?

RQ_4_: Among teams using TN, how is variation in coach engagement with the platform (e.g., login frequency and simulation use) associated with observed trends in student-athlete outcomes?

## 2. Materials and Methods

### 2.1. Setting and Design

This study will be conducted in collaboration with two high schools in North America, with data collected from two interscholastic teams at each high school. Two selected high schools will be randomly assigned to either the intervention group, which will use TN, or to a waitlist control group, which will not receive the intervention during the study period. Both groups will follow the rules set by their state’s interscholastic governing body and have access to standard school resources. Coaches will be recruited and informed consent will be obtained prior to student-athlete recruitment. Then, their athletes will be recruited accordingly. Informed consent will be obtained from parents or legal guardians before student-athlete recruitment, and assent will be obtained from all student-athletes. The interventional effect will be evaluated using a quasi-experimental design, and student-athlete outcomes will be measured at the beginning, midpoint, and end of the sport season. To gain an understanding of the experience of using TN, a subgroup of coaches and student-athletes will be recruited for interviews with open-ended questions. Altogether, we will analyze the qualitative and quantitative data using statistical and thematic analyses accordingly. While no monetary incentives will be provided, coaches and student-athletes will be invited to a brief end-of-season presentation where the research team will share key findings and practical takeaways. Participants will also receive a printed brochure with evidence-informed, actionable strategies and resources on mental health and team well-being. This protocol has been preregistered on the Open Science Framework (Registration DOI: 10.17605/OSF.IO/85S9G).

### 2.2. Participants

The study cohort will include high school student-athletes from two public schools, with two teams recruited from each school. Inclusion criteria are (1) full-time enrollment in the selected high schools; (2) on an interscholastic team; (3) age between 14 and 18 years at the beginning of the study; (4) fluency in English; and (5) access to a mobile device (iOS or Android). Head coaches of each participating team will also be recruited.

### 2.3. Sample Size Calculation

The present study is not powered for any confirmatory inference. The targeted roster sizes (approximately 15–25 athletes per team) are sufficient to evaluate feasibility and engagement and to provide preliminary clustering estimates (i.e., intraclass correlation coefficient). We will report these estimates with 95% confidence intervals. Precision will be limited by the small number of teams. Published intraclass correlation coefficient (ICC) values will also inform power for a future cluster-randomized trial.

### 2.4. Procedure

Coaches and high school student-athletes will be recruited from a purposive sample of two public high schools within a district that reflects a diverse demographic composition. Schools will serve as the unit of randomization and will be randomly assigned to either the TN intervention group or the waitlist control group. Four weeks prior to the start of the season, head coaches will be contacted via email, using the contact information provided by the district athletic director. Following pre-screening to confirm their coaching role, coaches will be invited to complete an online enrollment survey that includes the purpose of the study, its procedures, and an option to opt out. Coaches who consent to participate will be listed under the intervention or control condition. Two teams from each school will then be randomly selected for inclusion, resulting in a total of four participating teams. To prevent potential contamination, both teams from the same school will remain in the same condition, consistent with school-level group assignment. Teams in the intervention group will have access to TN throughout the season, whereas teams in the control group will serve as a waitlist control and receive access after the study is completed.

Parental consent and student-athlete assent will follow IRB-approved procedures appropriate for research with minors. Given that the study involves a non-clinical, educational mobile platform and poses no greater than minimal risk, the research team will seek for a passive (opt-out) parental consent process, consistent with school district research policies.

Parents or legal guardians will receive an informational letter via email two weeks before data collection, describing the study purpose, procedures, confidentiality protections, and voluntary nature of participation. The letter will include both an online opt-out form and contact information for the research team. Those who do not opt out will be considered to have provided consent. Student-athletes will then provide electronic assents prior to participation, with the option to withdraw at any time without penalty.

If more than 50% of parents or guardians on a selected team decline participation, that team will be replaced by another eligible team from the same school, which will inherit the school’s randomized condition to preserve the integrity of the cluster randomization. No re-randomization will occur at the team level. Parents or guardians of student-athletes in the waitlist control condition will receive similar study information but will be informed that their child(ren) will complete online surveys across the season and gain access to the TN mobile application after the season ends.

For the intervention group, a 30 min online pre-season training will be offered to orient participants to TN, including installation, initial setup, and core functions. Both the intervention and control groups will complete online surveys at three time points: the beginning of the season (baseline), mid-season, and the end of the season. Before each survey, participants will be reminded that their participation is voluntary, that they may withdraw at any time without penalty, and that their responses will be anonymous and not shared with coaches, parents, or school staff.

All survey data will be de-identified and stored on encrypted servers, accessible only to the research team. Coaches will not have access to individual student responses, only to aggregated, anonymized team-level summaries where appropriate. Neither personal-level data will be visible to schools nor to the TN developers.

Within two weeks of the postseason, coaches and student-athletes in the control group will be introduced to TN through a short tutorial and guided installation instructions via email. The study protocol and all related materials will be reviewed and approved by the Institutional Review Board prior to participant recruitment. All procedures will be conducted in accordance with the ethical principles outlined in the Declaration of Helsinki.

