### 2.9. Data Analysis

Analyses will use linear mixed-effects models (LMMs) estimated via REML to account for nesting (student-athletes within teams within schools) and to accommodate unbalanced repeated measures. Fixed effects will include condition (intervention vs. waitlist control), time (baseline, mid-, and end-season), and their interaction; random intercepts will be specified for team and school. Missing data will be handled by maximum-likelihood under MAR; if attrition exceeds 20%, multiple imputation will be used as a sensitivity analysis. Prespecified covariates include type of sport, gender, grade, and prior mental-health support. Given the pilot nature and very limited clusters, results will emphasize descriptive effect sizes with 95% CIs and ICCs/design effects rather than confirmatory *p*-values; where *p*-values are reported, we will control the false discovery rate (Benjamini–Hochberg) across outcomes.

Because cluster-randomized designs with few clusters are susceptible to chance baseline imbalances, baseline values of each outcome will be included as covariates in all longitudinal models. This baseline-adjusted specification is expected to improve precision and reduce bias attributable to baseline differences between conditions. As a sensitivity analysis, estimates will be examined with and without adjustment for multiple comparisons to evaluate the robustness of observed patterns. These analyses are intended to support transparent interpretation of exploratory findings.

Verbatim transcriptions of coach and student-athlete interviews will be analyzed using rapid content analysis to identify key usability insights, perceived benefits, and improvement opportunities related to the TN platform. The analysis will prioritize efficiency and practical relevance in studies with small samples, maintaining analytic rigor through structured coding and documentation. Two researchers will independently review transcripts, generate preliminary codes, and summarize key points within a shared matrix. Codes will then be grouped into higher-order categories to capture salient patterns in user experience and acceptability ([Bibr B6-behavsci-16-00268]). Findings will be summarized thematically but interpreted as exploratory, descriptive feedback rather than claims of thematic saturation. NVivo 12 ([Bibr B31-behavsci-16-00268]) will be used for data organization and coding.

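### As sequenced in Section 2.4, opt-out, team replacement and the baseline survey follow allocation, and baseline appears to follow TN training, so the baseline covariate may already carry an arm effect

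*Protocol article*

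**What the plan says.** The sequence is in Section 2.4 (Procedure) of the protocol article.

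- **Allocation.** "Schools will serve as the unit of randomization and will be randomly assigned to either the TN intervention group or the waitlist control group". There are two schools, hence one per arm.
- **Coaches.** "Four weeks prior to the start of the season, head coaches will be contacted via email". After consent, "Coaches who consent to participate will be listed under the intervention or control condition".
- **Teams.** "Two teams from each school will then be randomly selected for inclusion, resulting in a total of four participating teams".
- **Parents.** An opt-out letter goes out two weeks before data collection. Parents in the control condition are told that their children will answer surveys during the season and get the app once it is over.
- **Replacement.** "If more than 50% of parents or guardians on a selected team decline participation, that team will be replaced by another eligible team", taken from the same school and keeping that school's arm. The section gives preserving the integrity of the cluster randomisation as the reason.
- **Training.** In the intervention group "a 30 min online pre-season training will be offered to orient participants to TN, including installation, initial setup, and core functions". Section 2.5 also describes a pre-season orientation attended by coaches and student-athletes.
- **Surveys.** Both arms are surveyed at "the beginning of the season (baseline), mid-season, and the end of the season".

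Section 2.9 (Data Analysis) states that "baseline values of each outcome will be included as covariates in all longitudinal models". It expects this to improve precision and to reduce bias from baseline differences between conditions.

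**The concern.** Adjusting for baseline removes chance imbalance without distorting the comparison only if the baseline could not have been affected by allocation. Nothing in the article secures that. The survey is not placed before allocation, before the arm is disclosed or before TN training, and the wording on timing points the other way. The athletes who answer the survey may already have installed the app, attended an orientation, and have a coach who was offered training.

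The enrolled sample raises a related issue. Parents in the control arm decide on opt-out knowing that the app is deferred, and athlete assent and any team replacement come after that. If willingness to take part depends on the arm, the two groups can differ in ways that the model's covariates need not capture. Letting a replacement team inherit its school's arm does not address this.

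The study's output is effect sizes with 95% confidence intervals, meant to inform a later trial. A shift in those estimates would be carried forward.

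**Working it through.** The plan gives no effect size, SD or baseline correlation, so there is no figure of its own to reproduce. The check has three parts.

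**1. Order of events, from Section 2.4**

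| Step | Timing given | Arm known? |
|---|---|---|
| School allocation | before consenting coaches are listed by arm | – |
| Coach contact and consent | four weeks before season | not stated for coaches |
| Random draw of two teams per school | after listing by arm | not yet disclosed to parents |
| Parent letter and opt-out | letter two weeks before data collection | yes, for control parents |
| Team replacement | after opt-outs above 50% | yes, for control parents |
| TN training and installation | pre-season | yes |
| Baseline survey | beginning of season | yes |

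The order of the last two rows rests on the words pre-season and beginning of the season; there are no dates.

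**2. Effect of a shifted baseline on the adjusted estimate**

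Let d0 be the shift in the TN arm's baseline caused by training or by knowing the arm, and b the within-arm slope of outcome on baseline (equal to the correlation when SDs are equal). Then

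adjusted estimate = total effect − b × d0.

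Neither d0 nor b is in the documents. With assumed values, the change in SD units is:

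| b | d0 = 0 | d0 = 0.1 | d0 = 0.2 |
|---|---|---|---|
| 0.4 | 0 | −0.04 | −0.08 |
| 0.6 | 0 | −0.06 | −0.12 |
| 0.8 | 0 | −0.08 | −0.16 |

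A negative d0 reverses the signs. As an example, take a total effect of 0.30 SD and d0 = 0.20 SD. Then 0.30 − 0.5×0.20 = 0.20 SD, and 0.30 − 0.7×0.20 = 0.16 SD. A simulation of 400,000 subjects gave 0.20 and 0.161; adjusting for a baseline taken before the shift gave 0.30 in both cases.

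Section 2.9 also keeps baseline as a level of time. A contrast read as change from baseline would move by the whole of d0, here 0.30 − 0.20 = 0.10 SD.

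**3. How often replacement would occur**

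Section 2.3 gives rosters of about 15-25. More than 50% means at least 8 of 15, 11 of 20 or 13 of 25. The exact binomial probability per team, assuming independent opt-outs, is:

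| Opt-out rate (assumed) | 15 athletes | 20 athletes | 25 athletes |
|---|---|---|---|
| 20% | 0.4% | 0.06% | 0.04% |
| 30% | 5.0% | 1.7% | 1.8% |
| 40% | 21.3% | 12.8% | 15.4% |
| 50% | 50.0% | 41.2% | 50.0% |

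Replacement is therefore rare unless opt-out is high. Below the threshold, however, up to 7 of 15 or 12 of 25 athletes can be lost without triggering it.

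**The case against.** A reader might infer that the teams themselves are chosen after parents know the arm. The text does not support that: the two teams per school are drawn at random, and parents act only once a team has been selected. The arm-aware routes are opt-out, assent and replacement. Whether coaches know their arm when they consent is not stated.

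A reader might also infer that baseline adjustment must remove part of the TN effect. That is not shown either. The training is a 30-minute orientation that is offered, not required. The components likely to act, daily check-ins and repeated simulations, run through the season. The shift could be nil, or adverse through expectancy, and a full schedule outside the article may already put baseline first.

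On consequence, the design is called quasi-experimental and exploratory, with no confirmatory inference, and one school per arm confounds arm with school whatever the order of events.

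All of this limits the size of the point and stands. It does not dispose of it. The bias-reduction rationale in Section 2.9 needs a baseline untouched by allocation, and the sequence in Section 2.4 does not provide one. Dropping p-values does not correct a shifted estimate. The reason given for inheriting the arm claims more than the rule can deliver, however rarely replacement occurs.

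**Conclusion.** The point holds in limited form. On the article's wording, opt-out, any replacement and baseline follow school allocation and disclosure to control parents, and baseline appears to follow TN training. The covariate used in all longitudinal models may therefore carry an effect of training or of knowing the arm. The illustrative change in the adjusted estimate is 0.04-0.16 SD in size, for an assumed shift of 0.1-0.2 SD and slope of 0.4-0.8. It is zero if there is no shift, and its direction is not known. Arm-aware opt-out is a second route, which no figure in the documents allows one to quantify; replacement adds little unless refusal is around 40% or more. Two claims should be narrowed: that inheriting the arm preserves the randomisation, and that baseline adjustment reduces bias. The confounding of arm with school is a separate limitation and is unaffected.

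**What to change.** 1. In Section 2.4, require athlete assent and the baseline survey to be complete before TN training and installation in the intervention teams, at the same calendar point in both arms.
2. Where the schedule allows, send one parent letter covering both conditions, and reveal the school's arm only after opt-outs, any replacement and baseline are complete.
3. Delete the statement that inheriting the arm preserves the integrity of the randomisation; say that it keeps both teams of a school in one condition.
4. In Section 2.9, limit the bias-reduction claim to a pre-training baseline. If baseline cannot be moved, describe it as post-allocation and drop the claim.
5. Report opt-outs, assents and replacements by arm.

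**Cost.** No extra participants or instruments are needed, but the calendar is tight. A baseline one week before the season puts the parent letter at 1 + 2 = 3 weeks before it. That leaves 4 − 3 = 1 week after coach contact for consent and the team draw. If a replacement team gets its own two-week letter, its baseline would run past the season start, so item 2 may not always be achievable. TN training may start slightly later. The autonomy-support items (Section 2.8.6) ask about coaching in the season, so they need baseline wording if asked before it starts.
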